## Abstract

**Background:**

Acute respiratory tract infections (ARTI) are among the most frequent reasons for consultations in primary care. Although predominantly viral in origin, ARTI often lead to the prescription of antibiotics for ambulatory patients, mainly because it is difficult to distinguish between viral and bacterial infections. Unnecessary antibiotic use, however, is associated with increased drug expenditure, side effects and antibiotic resistance. A novel approach is to guide antibiotic therapy by procalcitonin (ProCT), since serum levels of ProCT are elevated in bacterial infections but remain lower in viral infections and inflammatory diseases.

The aim of this trial is to compare a ProCT-guided antibiotic therapy with a standard approach based on evidence-based guidelines for patients with ARTI in primary care.

**Methods/Design:**

This is a randomised controlled trial in primary care with an open intervention. Adult patients judged by their general practitioner (GP) to need antibiotics for ARTI are randomised in equal numbers either to standard antibiotic therapy or to ProCT-guided antibiotic therapy. Patients are followed-up after 1 week by their GP and after 2 and 4 weeks by phone interviews carried out by medical students blinded to the goal of the trial.

Exclusion criteria for patients are antibiotic use in the previous 28 days, psychiatric disorders or inability to give written informed consent, not being fluent in German, severe immunosuppression, intravenous drug use, cystic fibrosis, active tuberculosis, or need for immediate hospitalisation.

The primary endpoint is days with restrictions from ARTI within 14 days after randomisation. Secondary outcomes are antibiotic use in terms of antibiotic prescription rate and duration of antibiotic treatment in days, days off work and days with side-effects from medication within 14 days, and relapse rate from the infection within 28 days after randomisation.

**Discussion:**

We aim to include 600 patients from 50 general practices in the Northwest of Switzerland. Data from the registry of the Swiss Medical Association suggests that our recruited GPs are representative of all eligible GPs with respect to age, proportion of female physicians, specialisation, years of postgraduate training and years in private practice.

## Background

Acute respiratory tract infections (ARTI) are among the most frequent reasons for seeking ambulatory care [1]. ARTI in the context of this study include common cold, pharyngitis, tonsillitis, rhinosinusitis, tracheo-bronchitis, otitis media, acute exacerbations of asthma and of chronic obstructive pulmonary disease (COPD), and community acquired pneumonia. As much as 75% of antibiotics are prescribed for ARTI, despite the mainly viral origin [2-8].

Criteria often used in clinical practice to distinguish bacterial from viral infections of the respiratory tract include fever, dyspnea, purulent sputum, chest X-ray infiltrates, C-reactive protein, leucocyte count, and recovery of a pathogen from the respiratory tract or from blood cultures [9]. However, these are all non-specific symptoms and hence differentiation between viral and bacterial ARTI remains a diagnostic challenge [10]. Moreover, when antibiotic treatment is initiated, the optimal duration of antibiotic treatment for ARTI has not been determined [11,12]. In community acquired pneumonia an antibiotic treatment duration of 10 to 14 days is generally recommended, although data from intervention trials are lacking [13].

Unnecessary antibiotic use (i.e. number of prescriptions and duration of treatment) for ARTI not only increases drug expenditure [14] and the risk of adverse events [15], but also results in selection of resistant microorganisms [16]. Thereby, it constitutes an important public health problem [17]. For combating the increase in resistant infections a decrease of the excess antibiotic use is paramount [18]. There are only few intervention studies that have reported a successful reduction of antibiotic use in ambulatory care [19-25]. Most of these studies were not conducted in ARTI or have methodological limitations.

A novel approach to guide antimicrobial therapy is to prescribe antibiotics based on the level of biomarkers, specifically, calcitonin precursors, including procalcitonin (ProCT). Circulating levels of ProCT are elevated in systemic bacterial infections but remain relatively low in viral infections and inflammatory diseases [26,27]. In severe bacterial infections the use of ProCT significantly improves the sensitivity and specificity of the clinical diagnosis of infection [28]. A recent systematic review and meta-analysis found that ProCT is superior compared to C-reactive protein for the diagnosis of bacterial infections [29]. Most recently, we gathered evidence that both antibiotic prescription and treatment duration could be safely and markedly reduced in hospitalised patients with lower respiratory tract infections using ProCT-stewardship [30,31]. In successfully treated infections, circulating ProCT levels decrease in a log-linear pattern and have a plasma half life of 24 hours. In contrast, prolonged elevated plasma ProCT levels indicate adverse outcome [26,27].

Several studies indicate that the main reasons for antibiotic prescription in ambulatory patients with ARTI are non-medical and related to the physician-patient relationship, patients' expectations and beliefs about the benefit of antibiotics [32,33]. Thus, in theory a reduction of antibiotic prescriptions and duration can also be achieved by the implementation of guidelines [34]. However, in practice physician education and guidelines dissemination for ARTI management usually show no clinically relevant effect [25,35,36].

## Methods/Design

### Study aims

The objective of this trial is to evaluate, if a ProCT-guided diagnostic and therapeutic strategy leads to a similar outcome and reduced total antibiotic use for patients with ARTI in primary care compared to a standard approach recommended by current guidelines.

### Study design and setting

This is a prospective, randomised, controlled, open intervention trial in primary care with appropriate power calculation. Adult patients suffering from ARTI, for whom the treating general practitioner (GP) decides to give antibiotic treatment on the basis of evidence-based guidelines, are randomised to routine antibiotic therapy or ProCT-guided antibiotic treatment. The pathway by which patients are recruited and followed-up is given in Figure 1.

**Figure 1 F1:**
[figure not shown]
Summary of the trial design.

#### Ethical considerations

The Ethics Committee of the University Hospital Basel, Switzerland, approved the study protocol which is in compliance with the Helsinki Declaration. Written informed consent was obtained from all participating GPs. All recruited patients have to give written informed consent.

The trial is supervised by an independent monitoring board that is not involved in the design and conduct of the trial, or in the recruitment of patients. The board consists of a general internist in primary care, an infectious disease specialist and a pneumologist.

### Participants

We invited all GPs of two cantons (Basel-Stadt and Basel-Land) in the Northwest of Switzerland to participate in the trial. Of 345 GPs contacted, 53 working at 50 practices gave written informed consent and were included (Figure 2).

**Figure 2 F2:**
[figure not shown]
Flow diagram of recruited general practitioners.

From December 2004 GPs included in this study consecutively screen all eligible adults (aged 18 years or older) with symptoms (first experienced within the previous 28 days) of acute infection of the respiratory system. Inclusion criteria for patients are a consultation for common cold, pharyngitis, tonsillitis, rhinosinusitis, tracheo-bronchitis, otitis media, influenza, acute exacerbations of asthma or COPD, or community acquired pneumonia, the GPs intention to prescribe antibiotics on the basis of evidence-based guidelines, and written informed consent. Exclusion criteria for patients are antibiotic use in the previous 28 days, intravenous drug use, psychiatric disorders or inability to give written informed consent, not being fluent in German, severe immunosuppression (e.g. in HIV-infection, after solid organ transplantation or under chemotherapy), cystic fibrosis, active tuberculosis, and need for immediate hospitalisation. Study practices complete the trial after including 20 patients or at the anticipated end of the trial in December 2005.

### Randomisation

Allocation of patients to either treatment group is concealed by using a centralised randomisation procedure with a computer generated list produced by an independent statistician otherwise not involved in the trial. Randomisation is stratified by GP practice.

### Interventions

All participating GPs received instructions about the protocol and the details of the clinical trial in a 1-hour seminar. They were asked to consecutively enrol all patients with ARTI that they judge to be in need of antibiotic treatment according to guidelines. They were told how to call the central randomisation unit, and how to fill in the necessary study forms.

#### Evidence-based guidelines

[name] and MB developed guidelines for the management of ARTI based on evidence-based US-position papers which were endorsed by the Centers for Disease Control and Prevention, the American Academy of Family Medicine, the American College of Physicians, and the Infectious Disease Society of America [37-42]. We systematically searched MEDLINE and the Cochrane Library to update this evidence with recent controlled clinical trials. A panel of local primary care providers, infectious disease experts, and clinical epidemiologists reviewed the guidelines and made suggestions for adaptation to local conditions. We distributed the guidelines as a booklet (see ) and presented them in a 2-hour seminar to all participating GPs.

#### Procalcitonin test

We measure ProCT by using a newly developed time-resolved amplified cryptate emission (TRACE) technology assay (Kryptor PCT, Brahms, Henningsdorf, Germany). This assay is based on a sheep polyclonal antibody against calcitonin and a monoclonal antibody against katacalcin, which bind to the calcitonin and katacalcin sequence of calcitonin precursor molecules. The assay has an improved functional assay sensitivity of 0.06 μg/l – i.e., three to ten fold above normal mean values. Assay time is 19 min with 20–50 μl of plasma or serum. The test is performed at the central laboratory of the University Hospital Basel, and results can be communicated to participating GPs within 2–4 h depending on the location of the practice.

### Data collection and management

We obtained baseline data on all eligible GPs from the registry of the Swiss Medical Association. These data suggested that included GPs are representative of all eligible GPs with respect to age, years in private practice, years of postgraduate training, years since diploma, specialisation, and percentage of female physicians (Table 1).

**Table 1 T1:** Baseline characteristics of general practitioners

	**Study GPs**	All eligible GPs
	n = 53	n = 345

**Age **– median [IQR]	51 [42 – 55]	53 [47 – 58]
**Female physicians **– n (%)	9 (17)	64 (19)
**Specialisation**		
General medicine – n (%)	25 (47)	188 (54)
Internal medicine – n (%)	26 (49)	148 (43)
Other – n (%)	2 (3.8)	9 (2.6)
**Years in private practice **– median [IQR]	15 [6.2 – 20]	16 [9.0 – 23]
**Years of postgraduate training **– median [IQR]	8.8 [7.7 – 9.7]	8.9 [7.6 – 11]
**Years since diploma **– median [IQR]	25 [15 – 29]	26 [14 – 31]

When a participating GP intends to give antibiotic treatment to an eligible patient based on clinical criteria and the patient gives written informed consent, the GP calls the study centre and the patient is randomly allocated to one treatment group or the other. The GP then takes a blood sample from the patient and sends it by courier service to the laboratory of clinical chemistry at the University Hospital Basel. This laboratory measures ProCT in all patients. Additionally, the GP documents patient baseline data on signs and symptoms, diagnostic procedures, diagnosis, co-morbidity and prescribed medication.

Where patients are randomised to the ProCT-arm, GPs will be informed about ProCT results and given recommendations about appropriate antibiotic therapy within 2–4 h after the blood is taken depending on the location of the practice. A cut-off ProCT level of 0.1 μg/l is used to rule out a bacterial respiratory tract infection. This value is identical to the cut-off used for the evaluation of patients in the emergency department of the University Hospital Basel [30]. In patients with a ProCT level below 0.1 μg/l, the diagnosis of a bacterial respiratory tract infection is considered highly unlikely, and the GP is encouraged to look for viral or alternative causes. Accordingly, the use of antibiotics is discouraged. In patients with a ProCT level above 0.25 μg/l, a bacterial respiratory tract infection is considered the most likely diagnosis and the use of antibiotics is recommended. For ProCT levels from 0.1 to 0.25 μg/l, a bacterial infection is unlikely and antibiotic treatment is not advocated.

The GP then informs the patient about antibiotic treatment by phone. Patients in whom antibiotics are given will be asked to use a delayed prescription or to come back to the practice to pick up the antibiotic there. For patients in whom antibiotics are withheld based on ProCT levels of 0.25 μg/l or below, a follow-up measurement of ProCT within 24 hours is mandatory. If the ProCT level on this initial follow-up is >0.25 mg/l or if it has increased by more than 50% from its initial value without clinical improvement of the patient, the use of antibiotics is recommended.

In the ProCT group, all patients treated with antibiotics will be reassessed at Day 3. Discontinuation of antibiotic treatment is recommended if the ProCT level has decreased at least to 0.25 μg/l or below.

GPs draw blood samples and document therapy at each follow-up visit. They also collect information on days with restrictions and days off work at 1 week (6–8 days) after randomisation for all patients. Medical students, blinded to treatment allocation of patients and to the goal of the trial, will conduct standardised follow-up interviews at 14 and 28 days by phone. The patient flow will be monitored according to current guidelines and in agreement with the CONSORT statement [43]. We will use Teleform^® ^(Cardwell, Cardiff, GB) for data entry.

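### The 24-hour restart threshold is printed as 0.25 mg/l, 1000 times the 0.25 μg/l used everywhere else in the ProCT algorithm

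*Protocol article*

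**What the plan says.** The ProCT algorithm is set out in the protocol article under Methods/Design, Data collection and management. It uses the number 0.25 in four rules.

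- **Initial result, treat.** "In patients with a ProCT level above 0.25 μg/l, a bacterial respiratory tract infection is considered the most likely diagnosis", and antibiotics are recommended.
- **Initial result, withhold.** "For ProCT levels from 0.1 to 0.25 μg/l, a bacterial infection is unlikely and antibiotic treatment is not advocated". Below 0.1 μg/l they are discouraged. The 24-hour re-measurement is compulsory for everyone in these two bands: "For patients in whom antibiotics are withheld based on ProCT levels of 0.25 μg/l or below".
- **24-hour re-measurement, restart.** Antibiotics are recommended on either of two conditions. The absolute one is "If the ProCT level on this initial follow-up is >0.25 mg/l". The relative one is "or if it has increased by more than 50% from its initial value without clinical improvement of the patient".
- **Day 3, stop.** "Discontinuation of antibiotic treatment is recommended if the ProCT level has decreased at least to 0.25 μg/l or below".

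Three of the four are in μg/l. Only the absolute condition at 24 hours is in mg/l. The assay's functional sensitivity, under Procalcitonin test, is also in μg/l (0.06), as is the 0.1 rule-out level. Nothing in the article explains or corrects the different unit.

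**The concern.** Every enrolled patient is someone the GP had already judged to need antibiotics. Where the ProCT result leads to withholding, the 24-hour check is the stated route back to treatment, so it is the safety rule of the experimental strategy. The trial's hypothesis is that clinical outcome is no worse under that strategy.

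If the absolute condition is inert as printed, the algorithm contradicts itself. A value just above 0.25 μg/l leads to an antibiotic recommendation at the first measurement and does not trigger stopping at Day 3. At 24 hours the same value leads to no recommendation unless the relative condition is also met. The question is whether the relative condition covers the gap; if it does not, the misprint changes the advice for identifiable patients.

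**Working it through.** **Inputs**, all from Data collection and management:

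- printed 24-hour absolute threshold: above 0.25 mg/l
- patients entering the check: initial ProCT at or below 0.25 μg/l
- initial treatment threshold: above 0.25 μg/l
- relative condition at 24 hours: rise of more than 50%, no clinical improvement

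**Step 1: unit conversion.** 1 mg/l = 1000 μg/l, so 0.25 mg/l = 0.25 × 1000 = 250 μg/l. The ratio to the other thresholds is 250 / 0.25 = 1000.

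**Step 2: can the printed absolute condition act?** The highest starting value is 0.25 μg/l. To exceed 250 μg/l the level must rise more than 250 / 0.25 = 1000-fold, that is by more than (1000 − 1) × 100 = 99,900%. Any non-improving patient with such a rise has already met the relative condition. The printed absolute condition therefore adds nothing, apart from the theoretical case of a rise of more than 1000-fold in a patient who is improving.

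**Step 3: does the relative condition cover the gap?** For a non-improving patient with initial value *s*, it triggers above 1.5 × *s*. It catches every crossing of 0.25 μg/l if 1.5 × *s* ≤ 0.25, that is if *s* ≤ 0.25 / 1.5 = 0.167 μg/l. For *s* above 0.167, 24-hour values above 0.25 and up to 1.5 × *s* are missed:

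| Initial value (μg/l) | 1.5 × initial (μg/l) | 24-hour values missed as printed (μg/l) |
|---|---|---|
| 0.10 | 0.150 | none |
| 0.15 | 0.225 | none |
| 0.18 | 0.270 | above 0.25, up to 0.27 |
| 0.20 | 0.300 | above 0.25, up to 0.30 |
| 0.22 | 0.330 | above 0.25, up to 0.33 |
| 0.25 | 0.375 | above 0.25, up to 0.375 |

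**Worked example.** A non-improving patient goes from 0.20 to 0.28 μg/l. The rise is (0.28 − 0.20) / 0.20 = 40%, so the relative condition is not met. The value is below 250 μg/l, so the printed absolute condition is not met either, and no antibiotics are recommended. With the threshold at 0.25 μg/l they would be, since 0.28 > 0.25.

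**Step 4: improving patients.** If the clause about clinical improvement qualifies only the relative condition, a patient who crosses 0.25 μg/l while improving gets a recommendation under μg/l and none as printed, whatever the size of the rise (short of the 1000-fold case in Step 2).

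**Step 5: sample size.** The stated 275 per group rests on a one-day margin, a standard deviation of 4 days, 5% type I error and 90% power. It reproduces at 275 with a one-sided 5% level, and 275 / 0.9 = 305.6 rounds up to the stated 306. No ProCT threshold enters it.

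**The case against.** The strongest reply is that this is a one-character misprint no reader would act on. All other ProCT levels are in μg/l, and the sentence just before uses 0.25 μg/l for the same patients. That stands as to intent: μg/l is plainly what was meant. It does not make the printed rule right, and the number is a treatment threshold rather than background text.

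The letter could also have been altered in typesetting or text conversion. This cannot be fully excluded, but μ is rendered correctly in the preceding sentence and the following paragraph, so conversion is an unlikely cause.

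A third reply is that no operational harm is shown. ProCT is measured in the hospital laboratory and GPs are sent recommendations. With 213 patients recruited by April 2005, the trial was already running on working materials that are not shown. This is fair: nothing suggests those materials are wrong or that any patient was managed under mg/l. It limits the claim to the text and makes the remedy a check.

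Fourth, the rule to treat above 0.25 μg/l is not expressly confined to the first sample, so it might be read as still applying at 24 hours. But it appears in the account of the initial result, and the 24-hour check has its own rule. If both apply, they conflict.

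Finally, the affected groups are narrow and uncounted, and the improving group depends on how one clause is read. If that clause governs both conditions, the improving group drops out; the non-improving group remains.

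**Conclusion.** The point holds. The absolute threshold of the 24-hour restart rule is printed 1000 times too high (250 against 0.25 μg/l) and contradicts the other 0.25 rules in the same section. Followed literally, it cannot act in practice.

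The advice changes for two groups:

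- non-improving patients who start above 0.167 and up to 0.25 μg/l and cross 0.25 μg/l with a rise of at most 50%
- patients who cross 0.25 μg/l while improving, assuming the improvement clause qualifies only the relative condition

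Non-improving patients who start at or below 0.167 μg/l and cross 0.25 μg/l are still caught by the relative condition. The article gives no figures from which the size of either group could be estimated. The non-inferiority margin, sample size, endpoints and analysis are untouched. It should be fixed because it sits in the safety rule of the intervention, not because the intended meaning is in doubt.

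**What to change.** Change the 24-hour threshold from mg/l to μg/l, so that it reads as above 0.25 μg/l. Because recruitment is under way, also confirm that whatever generates the 24-hour recommendations sent to GPs (laboratory report templates, recommendation forms, GP instructions) uses the same unit.

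The cost is one unit in one sentence and one check of working materials. While the sentence is open, it would help to state whether the improvement clause applies to both conditions or only to the relative one.

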### Adverse events

Any serious adverse event is reported by fax to the principle investigator within 24 hours. We define a severe event independent of group allocation as hospitalisation for any reason, any complication related to infection such as sepsis, abscess etc., or allergic reaction due to the received therapy, or death that occurs within 28 days following the inclusion of the patient into the trial.

### Outcomes and hypotheses

The primary outcome is days with restrictions from ARTI within 14 days after randomisation. Secondary outcomes are antibiotic use in terms of antibiotic prescription rate and duration of antibiotic treatment in days, days off work and days with side-effects from medication within 14 days, and relapse rate from ARTI within 28 days after randomisation.

Our hypothesis is that the clinical outcome for patients with ARTI will be no worse under ProCT-guided treatment, but patients with ProCT-guided treatment will have lower total antibiotic use; specifically a 20% lower antibiotic prescription rate and a 20% shorter antibiotic duration compared to patients treated under the standard approach.

### Sample size considerations

This is a non-inferiority trial. We aim to show that on average ProCT-guided antibiotic management leads to at most one day more with restrictions than a standard approach. We consider a type I error rate of 5% and a type II error rate of 10% (i.e. 90% power) appropriate in this situation. In a previous trial in patients with acute respiratory tract infections (ISRCTN57824788), the standard deviation in the number of days with restrictions from ARTI was 4 days for those patients prescribed antibiotics. Given this previous estimate of the variability in the primary outcome, 275 patients are needed per treatment group [44]. Allowing for a loss to follow-up of 10% gives 306 patients per treatment group, or a total of 612 patients. This sample size will allow us to estimate the reduction in antibiotic use between the two arms to within ± 6%.

With a maximum of 20 patients recruited per practice we will probably need at least 35 participating general practices. To assess between-GP-variability in a sensitivity analysis, we will need a minimum of 10 patients (preferably 15) recruited per practice.

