### Statistical analysis

With a non-inferiority trial, an intent-to-treat analysis is not necessarily conservative. For the primary outcome, we will need to provide several intent-to-treat analyses under different assumptions about patients who do not complete the trial, and a per-protocol analysis. Per-protocol analyses are planned for all secondary outcomes [44].

All outcomes will be analysed by a generalised linear model, assuming an appropriate distribution for each outcome and using the same set of covariates. These covariates will be: age, sex, education and a baseline score of the degree of restricted activity reported by the patient. 95% confidence intervals will be reported for the difference between treatment groups.

For the primary outcome, the assumed distribution will be normal; that is, analysis will be by multivariate linear regression. As a sensitivity analysis, the GP will be added to the model as a random effect and the model re-fit to the data from all GPs with only one GP per practice and with at least 10 patients per GP. Our experience from a previous trial (ISRCTN57824788) is that the difference between GPs has little influence on patient reported outcomes.

For secondary outcomes, assumed distributions will be binomial (i.e. for prescription of antibiotics) or normal (i.e. duration of antibiotic treatment). Duration of antibiotic treatment will be analysed only for those patients who receive antibiotics. We will also report a confidence interval for the difference in the antibiotic prescription rate between treatment groups. As a sensitivity analysis, we will repeat this calculation using a method appropriate for a cluster sample, where each GP forms a cluster and using only data from GPs with one GP per practice and with at least 10 patients per GP.

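### The 275 per group rests on a one-sided 5% test, but the only interval level the protocol names is 95%; the two are not reconciled, and power is about 83% if that interval decides

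*Protocol article*

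**What the plan says.** The Sample size considerations section of the protocol article declares the design ("This is a non-inferiority trial") and gives the aim as showing that, on average, "ProCT-guided antibiotic management leads to at most one day more with restrictions than a standard approach". The endpoint is fixed under Outcomes and hypotheses: "The primary outcome is days with restrictions from ARTI within 14 days after randomisation".

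The error rates are set in one sentence: "We consider a type I error rate of 5% and a type II error rate of 10% (i.e. 90% power) appropriate in this situation". Sidedness is not mentioned. The variability comes from an earlier trial, in which "the standard deviation in the number of days with restrictions from ARTI was 4 days for those patients prescribed antibiotics". From these inputs the section concludes that "275 patients are needed per treatment group", which becomes 306 per group and 612 in total after allowing for 10% loss to follow-up.

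The Statistical analysis section, in the paragraph on the models for all outcomes, states: "95% confidence intervals will be reported for the difference between treatment groups". No other confidence level and no one-sided bound appears in the article. No sentence says which limit of which interval is to be compared with the 1-day margin.

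**The concern.** In a non-inferiority trial the conclusion is usually read from a confidence limit set against the margin, so the interval and the error rate used for sizing should be the same test. A two-sided 95% interval corresponds to a one-sided 2.5% test. A one-sided 5% test corresponds to a two-sided 90% interval. The article gives a 5% error rate in one section and a 95% interval in the next, and a reader would naturally pair them. If the 275 was derived from the one-sided 5% test, that pairing is wrong and the stated 90% power does not belong to the interval that will be reported.

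The primary conclusion is at stake. An observed difference that falls between the two cut-offs would be non-inferior by the rule used for sizing and not non-inferior by the interval in the report. The protocol does not state which reading prevails.

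**Working it through.** **Inputs.** Margin 1 day, SD 4 days, type I error 5%, power 90%, 275 evaluable and 306 randomised per group, 10% loss (all from Sample size considerations); equal allocation (Abstract). One assumption is mine: a true difference of 0 days. The article does not state it, but it is consistent with the 275.

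**Step 1: reproduce the stated figure.** n per group = 2 × (z_α + z_β)² × SD² / margin², with z_β = 1.28155 for 90% power.

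- One-sided 5%: 2 × (1.64485 + 1.28155)² × 16 / 1² = 274.04, rounded up to **275**. This matches, and a calculation based on the t distribution also gives 275.
- Loss to follow-up: 275 / 0.9 = 305.6, rounded up to **306**; 2 × 306 = **612**. Both match.

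**Step 2: try the other readings.**

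- One-sided 2.5% (upper limit of a two-sided 95% interval): 2 × (1.95996 + 1.28155)² × 16 = 336.2, rounded up to 337 (338 with the t distribution). No match.
- Two-sided equivalence at 5%: about 347. No match.

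Of the readings tried, only the one-sided 5% test gives the sizing figure.

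**Step 3: power under each decision rule.** The standard error of the difference at 275 per group is 4 × √(2/275) = 0.341 days, so margin / SE = 2.932. At 306 per group it is 4 × √(2/306) = 0.323 days, so margin / SE = 3.092.

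| Decision rule | 275 evaluable per group | 306 evaluable per group |
|---|---|---|
| One-sided 5% (two-sided 90% interval) | Φ(2.932 − 1.645) = 90.1% | Φ(3.092 − 1.645) = 92.6% |
| One-sided 2.5% (two-sided 95% interval) | Φ(2.932 − 1.960) = 83.4% | Φ(3.092 − 1.960) = 87.1% |

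The noncentral t distribution gives 90.0% and 83.3% at 275, and 92.6% and 87.0% at 306. On the 95% interval at 275 per group the type II error is 100% − 83.4% = 16.6%, against the stated 10%.

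**Step 4: where the rules disagree.** With SE 0.341, non-inferiority is shown if the observed difference (ProCT minus standard) lies below:

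- 1 − 1.960 × 0.341 = 0.33 days on the 95% interval;
- 1 − 1.645 × 0.341 = 0.44 days on the 90% interval.

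Differences between about 0.33 and 0.44 days change the conclusion. If the true difference is 0, this happens in 90.1% − 83.4% = 6.7% of trials.

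**Step 5: what would restore 90% on the 95% interval.** By numbers alone, 337 evaluable per group, which is 337 / 0.9 = 374.4, so 375 per group and 750 in total. By covariate adjustment alone, the covariates would have to explain about 1 − 275 / 336.2 = 0.18 of the outcome variance. The article gives no figure for this, and its sample size calculation takes no credit for adjustment.

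**The case against.** The strongest reply is that the shortfall depends on a decision rule the article does not state. It says that 95% intervals will be reported, in a sentence covering every outcome, and reporting an interval is not the same as deciding on it. The only error rate set for the primary hypothesis is 5%, the hypothesis is one-directional, and the 275 shows which test was meant. On that reading the power is 90%, as stated, and the 95% interval is for estimation. The word two-sided is also not in the text: a one-sided 95% bound would match the sizing exactly.

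Most of this stands. A reader might infer that the sample size was miscalculated; it was not, since 275, 306 and 612 all reproduce. A reader might infer that the trial is underpowered; the documents do not establish that, because the 83% is conditional on using the 95% limit and ignores the planned covariates. A reader might infer that the error rate is open to choice once the data are seen; that goes too far, since 5% is prespecified and the 275 points to its one-sided use. Judging on the 95% limit is also the stricter rule, so it cannot increase false claims of non-inferiority.

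It could also be said that a journal article leaves the decision rule to the full protocol or analysis plan. That answers a complaint of missing detail, but not this one. The article itself fixes an error rate with its sample size, and an interval level, and on the ordinary reading they describe different tests. No later document can keep the 95% interval as the decision interval and also keep the stated 90% power at 275 per group without relying on a gain from the covariates.

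**Conclusion.** The point holds as an unreconciled mismatch between Sample size considerations and Statistical analysis. It is neither an arithmetic error nor a demonstrated loss of power. If non-inferiority is judged at one-sided 5%, the stated 90% stands. If it is judged on the upper limit of the two-sided 95% interval, power is about 83% at 275 evaluable per group and about 87% if nobody is lost. These figures rest on SD 4 days, a true difference of 0, the ordinary two-sided reading of the 95% interval, and no gain from covariates.

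It should be fixed, because it concerns the primary conclusion and the correction is cheap. It is not critical: the two rules differ only in a band of about 0.1 day in the observed difference, and the 95% reading errs on the cautious side.

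**What to change.** Before any between-group analysis, align the two sections by one of these routes.

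- **(a)** State that non-inferiority is concluded if the upper limit of the two-sided 95% confidence interval for ProCT minus standard is below 1 day. Restate the type I error as one-sided 2.5%, and the power as about 83% for 275 evaluable patients per group before covariate adjustment.
- **(b)** State that the 5% type I error is one-sided. Name the two-sided 90% interval (equivalently, the one-sided 95% upper bound) as the decision interval, and label the 95% interval descriptive. The 275 and the 90% then stand unchanged.

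Both are acceptable. Route (a) keeps the interval already promised, at the price of a less favourable stated power. Route (b) keeps every stated figure. Either costs one or two sentences and no additional patients.
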